### Sample size calculation

A total of 63 individuals by each group of treatment will allow detecting, in numerical variables, differences between pairs of group mean in a magnitude corresponding to 50% of the standard deviation (an effect size of 50%) with a probability of 80%, keeping the type I error at a 5% level. By taking into account an attrition rate of 25%, it would be necessary to include 78 individuals in each group. The calculation has been done using G*Power 3.1.

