### Statistical analysis

Numerical variables will be summarised with means and standard deviations and categorical ones with percentages. Those numerical variables showing a distribution very far from the normal one will be transformed for getting resulting distributions close to the normal one, or in the opposite case, they will be summarised by using percentiles. For the graphical representation of the numerical variables’ distribution in each treatment group, we will use box and whisker plots. For representing categorical variables, pie charts will be used. In order to test the equality of means for numerical variables, we will apply the Student’s t, if the corresponding distributions are not far from the normal one. In the opposite scenario, we will calculate the Wilcoxon–Mann–Whitney statistics. For testing the association between qualitative variables, we will use Chi-squared statistics, if it is allowed by the observed frequencies in the associated joint distribution. On the contrary, we will re-categorise these variables for reducing them to dichotomous ones, if necessary, and will apply the Fisher exact test. As a function of the observed response to the treatment in numerical variables or the observed change in them, we will build several definitions of success/failure for the result of treatment in individuals. We will fit logistic regression models for predicting the success of the treatment by using the previously mentioned definitions. In these models, those variables which show a statistically significant relationship with the corresponding response variables in the univariate analysis and the variable selection procedures will be included. These models will provide us, as a by-product, odds ratio values for estimating the comparative risk of success associated with each explanatory variable corrected by the presence of the other variables included in them. We will obtain estimates for the sensitivity/specificity of predictive rules derived from these models. It will be considered as statistically significant *p*-values lower than 0.05. Data analysis will be carried by using the R statistical software.

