### Outcomes variables

All variables will be measured before the intervention, after the intervention (week 11), at six months, and a year. Flowchart of the study can be seen in Fig. 3.

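### Where success is defined by change from baseline, the planned success models can present regression to the mean as a predictor of treatment success, and the entry rule does not keep randomised arm in the model

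*Protocol article*

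**What the plan says.** All of this stands in the Statistical analysis section of the protocol article, apart from the measurement schedule.

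- Success is to be defined in more than one way: "As a function of the observed response to the treatment in numerical variables or the observed change in them, we will build several definitions". Response and change are both allowed, and no cut-off is given.
- The purpose of the models is stated: "We will fit logistic regression models for predicting the success of the treatment by using the previously mentioned definitions".
- Entry is data-driven. The models take in "those variables which show a statistically significant relationship with the corresponding response variables in the univariate analysis", together with formal variable selection.
- The output is described as "odds ratio values for estimating the comparative risk of success associated with each explanatory variable corrected by the presence of the other variables". Sensitivity and specificity of the resulting predictive rules follow.
- Under Outcomes variables: "All variables will be measured before the intervention, after the intervention (week 11), at six months, and a year". A baseline value of every scale that could define success is therefore available as a candidate.

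The text does not list the candidate predictors, say whether the arms are pooled, or state or exclude interaction terms.

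**The concern.** An odds ratio for one variable, adjusted for the others, shows who improves. It does not show in whom the programme does better than usual care physiotherapy. In a randomised trial with an active comparator, the second question needs arm in the model and a term for arm by variable. The stated entry rule admits variables on significance, so it guarantees neither.

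The baseline of the scale that defines success is a special case. Change is follow-up minus baseline, so baseline sits inside the response with a negative sign. A patient who scores badly at entry tends to score nearer the mean later, in either arm and without any treatment effect. Screening on univariate significance favours this association. The problem is separate from optimism caused by selection: it arises with a single prespecified definition and a single prespecified predictor.

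At stake is a report that patients with worse initial quality of life, pain or catastrophising are those in whom treatment succeeds, with a predictive rule attached, when the data would look the same if the programme did nothing.

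**Working it through.** **Plan's own figure.** The plan gives no figure for the logistic models. Its sample size is for a comparison of two means at 0.5 SD, "with a probability of 80" per cent and "keeping the type I error at a 5% level". Taking the test as two-sided: n = 2 × (1.960 + 0.842)² / 0.5² = 62.8, so 63 per group, as stated. That gives N = 2 × 63 = 126 evaluable. Enrolment is 2 × 78 = 156. A 25% loss from 78 leaves 58.5 per group; 59 per group gives N = 118.

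**Algebra.** Let B and F be baseline and follow-up with SD 1 and correlation r.

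- Cov(B, F − B) = r − 1
- Var(F − B) = 2(1 − r)
- Corr(B, F − B) = −√((1 − r)/2)

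This is −0.50 at r = 0.5, −0.39 at 0.7, −0.32 at 0.8 and −0.22 at 0.9. If change were kept continuous, a correlation of about 1.96/√126 = 0.17 would reach p < 0.05. Dichotomising loses some of that sensitivity, hence the simulation.

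**Simulation under the null.** Baseline and follow-up are bivariate normal with no arm effect and no effect modification. Success is a gain of at least the cut-off. The figure is the share of trials in which poorer baseline is significant at 0.05. Assumed, because the documents do not give them: r, the cut-off and any time trend common to both arms. Under this model only the cut-off minus the trend matters, so a 0.3 SD cut-off with a 0.3 SD trend is the same case as a cut-off of 0 without a trend.

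N = 126:

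| r | 0.3 SD trend, cut-off 0.3 / 0.5 SD (2,000 trials) | No trend, cut-off 0 / 0.5 SD (1,000 trials) |
|---|---|---|
| 0.5 | 99.8% / 99.9% | 99.8% / 99.5% |
| 0.6 | 99.0% / 98.3% | 98.4% / 97.0% |
| 0.7 | 94.4% / 94.6% | 94.0% / 90.9% |
| 0.8 | 80.9% / 80.7% | 82.7% / 73.3% |
| 0.9 | not run | 51.6% / 33.5% |

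With the 0.3 SD trend, the median odds ratio per SD of worse baseline falls from about 2.6 at r = 0.5 to 1.7 at r = 0.8.

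The first column is from a model with baseline alone; the second also contains arm. Adding arm as a main effect does not remove the association: with the 0.3 SD trend and r = 0.8, a repeat run of 1,500 trials gave 83.0% / 82.1% without arm and 82.9% / 81.7% with it. The arm-by-baseline interaction rejected in 3.7-5.0% of trials in the first setting and 3.6-6.0% in the second, close to nominal.

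**Sensitivity to the assumptions.**

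- N = 118, no trend, 0.5 SD cut-off: 99% at r = 0.5, 89% at 0.7, 70% at 0.8, 31% at 0.9.
- N = 156, same definition: 100%, 95%, 81%, 39%.
- One arm fitted alone (N = 63), same definition: 88%, 60%, 39%, 16%.
- 1 SD cut-off, no trend, N = 126: 97% at r = 0.5, 72% at 0.7, 40% at 0.8.
- 30% relative reduction (assumed pain mean 55, SD 20), N = 126: 39%, 3% and 0% at r = 0.5, 0.7 and 0.8.
- Success as an attained follow-up level, N = 126: poor baseline predicts success in 0% of trials, and good baseline does so in 99-100%.

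The coefficient for arm itself kept a false-positive rate of at most about 6% throughout.

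**The case against.** The strongest reply is that the text leaves much of this open. Change is only one of two permitted bases for success. No candidate predictors are named, and most of the items listed under Initial personal and sociodemographic variables are not arithmetically tied to change in a questionnaire score. Interactions are neither planned nor ruled out, and a fuller analysis plan may settle them. The models can also be read as prognostic, in which case an association between baseline and change is real and not a false positive. No stated objective is to find which patients benefit more, and the Discussion links a change of practice to between-group effect sizes.

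Much of this stands, and it rules out several stronger readings that a reader might infer:

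- *Success is always change from baseline.* Not supported; response is the other branch.
- *The plan is confined to main effects.* Not supported; it is silent on interactions.
- *A spurious baseline predictor is near-certain in this trial.* Not supported; the rate depends on a correlation and a cut-off that the documents do not give, and across plausible choices it runs from about 0% to 100%.
- *The primary result is biased.* Not supported; the comparison of means between randomised groups does not use these models.
- *The rules will decide who is referred.* The article does not say so.

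The reply does not answer what the text does fix: change is an allowed basis for success, entry is by significance, and each odds ratio is tied to treatment success. Nor does the response branch offer a way out if it means an attained level, because baseline is then an almost certain null predictor in the opposite direction. Several definitions could therefore yield contradictory rules from the same patients.

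**Conclusion.** The point holds in conditional form. Where success is an absolute change and the same scale's baseline is screened, the plan as written will usually report poor baseline as a predictor of treatment success when there is no treatment effect. For N = 126 and a 0.3 to 0.5 SD cut-off, with or without a modest common time trend, the rates are about 99% at r = 0.5, 90-96% at r = 0.7, 70-84% at r = 0.8 and 35-50% at r = 0.9. They rest on bivariate normal scores with equal SDs and on an assumed correlation, cut-off and trend. They are lower with a 1 SD cut-off, a relative-reduction definition, fewer analysed patients or separate arms.

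The fault lies in how the secondary predictor models are specified and read. It is worth correcting before analysis, but it does not threaten the randomised comparison.

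**What to change.** Amend the description of the success models as follows.

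1. Force randomised arm and the baseline value of the scale that defines success into every success model; do not screen either. Arm alone does not cure the problem. The baseline term is needed so that other variables correlated with it do not pick up the same artefact.
2. Treat that baseline as an adjustment covariate and do not report it as a predictor of treatment success.
3. Label main-effect odds ratios, and the predictive rules derived from them, as prognostic.
4. Make any claim about who benefits more from the programme only from an arm-by-variable interaction.

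The cost is some wording and a few extra model terms, with no new data. The real downside is that interaction tests have low power at this sample size, so fewer predictors of benefit are likely to be reported.

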#### Main outcomes variables

The primary outcome measure will be the difference between groups in health-related quality of life changes at different times. The Spanish version of the health Survey SF-36 V2 will be used [61, 62]. SF-36 is a 36-item scale built to assess health status and quality of life. It produces a profile of eight levels of functional health and wellness scores, as well as a summary of psychometric-based mental and physical health. Each scale transforms directly into a scale of 0–100. Higher scores indicate a better quality of life in general.

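### The only covariate-adjusted estimates the protocol describes come from scores cut into success/failure, which for the arm effect costs about 20 points of power or more against a linear model of the same score

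*Protocol article*

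**What the plan says.** The Sample size calculation section sizes the trial on numerical outcomes, with 63 patients per arm and 80% power. The target is given as "differences between pairs of group mean in a magnitude corresponding to 50% of the standard deviation", and the error rate as "keeping the type I error at a 5% level". The primary outcome, in Main outcomes variables, is the between-group difference in SF-36 change, and of the SF-36 scales the article says "Each scale transforms directly into a scale of 0–100". Most secondary outcomes are also numerical scores: VAS 0–100, PCS 0–52, TSK-11 11–44, Central Sensitisation Inventory 0–100 and Roland–Morris 0–24.

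The Statistical analysis section compares means with Student's t or, for clearly non-normal data, Wilcoxon–Mann–Whitney. Neither test is adjusted. From the numerical responses or their changes, the section then says "we will build several definitions of success/failure for the result of treatment in individuals". Logistic regression is the method it names for analysing them: "We will fit logistic regression models for predicting the success of the treatment by using the previously mentioned definitions". Variables enter these models through univariate significance and selection procedures. The resulting odds ratios, each corrected for the other variables in the model, are called a by-product. Sensitivity and specificity of predictive rules are also to be estimated. No regression of an uncut score is named, and no cut-point is given.

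**The concern.** The unadjusted tests use the whole score. Once another variable is allowed for, the response becomes a yes/no cut of that score. A patient just over the cut then counts the same as one far over it, and that distinction is lost to every coefficient in the model.

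Two things are at stake. First, an adjusted arm effect or a predictor of response is harder to detect than the data allow. Second, if arm is in the model, a non-significant adjusted odds ratio could sit beside a significant t-test of the same score and be read as a conflict, when the cut alone may explain it. Both would hold even if the cuts and covariates were fixed in advance; the issue is the scale of the response.

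**Working it through.** **Inputs from the protocol article.** 63 per arm, difference 0.5 SD, type I error 5%, power 80% (Sample size calculation); 1:1 allocation (Methods and study design). Sidedness is not stated. Two-sided is used because it reproduces 63, whereas one-sided gives 50–51.

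**Assumptions.** Scores are normal with equal SD in both arms. Cut-points and success rates are not in the article, so a range is shown. The covariate correlation in step 4 is also assumed.

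**1. The stated sample size.** n per arm = 2(1.960 + 0.842)² / 0.5² = 2 × 7.85 / 0.25 = 62.8, so 63. This matches. The exact t-test power at 63 per arm is 79.5%.

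**2. The same effect after a cut.** For a cut c, in SD units above the control mean, control success is p0 = 1 − Φ(c) and experimental success is p1 = 1 − Φ(c − 0.5). With mean proportion p̄,

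power = Φ{[(p1 − p0) − 1.96 √(2p̄(1 − p̄)/n)] / √([p0(1 − p0) + p1(1 − p1)]/n)}.

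At the most favourable cut, c = 0.25: p0 = 0.401, p1 = 0.599, difference 0.197. The two standard errors are √(0.5/63) = 0.0891 and √(0.4805/63) = 0.0873. Power = Φ[(0.1974 − 0.1746)/0.0873] = Φ(0.26) = 60.3%.

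| Control v experimental success | Power, 63 per arm | n per arm for 80% |
|---|---|---|
| Uncut score (t-test) | 79.5% | 63–64 |
| 40% v 60% | 60.3% | 100 |
| 50% v 69% | 59.3% | 102 |
| 30% v 49% | 59.0% | 103 |
| 20% v 37% | 54.5% | 115 |
| 10% v 22% | 43.6% | 152 |

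The loss runs from 79.5 − 60.3 = 19 points to 79.5 − 43.6 = 36 points. As a cross-check, the relative efficiency of a median split is 2/π = 0.64, and 63/100 = 0.63. Simulated Wald, score and likelihood-ratio tests from a logistic model with arm only gave 58–64% for cuts near the centre, so the formula is a fair guide.

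**3. Fewer patients.** If 25% of the planned 78 are lost, 78 × 0.75 = 58.5 remain. At 58 per arm the t-test has 76.1% power and the best cut 56.7%.

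**4. Adjusted models.** Simulated trials with 63 per arm, an arm effect of 0.5 SD and one baseline covariate with within-arm correlation r gave this power for arm:

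| r (assumed) | Linear model, uncut score | Logistic, 40% v 60% cut | Logistic, 16% v 31% cut |
|---|---|---|---|
| 0.25 | about 83% (runs 82–84%) | about 63% | 52% |
| 0.5 | 89–91% | 69% | 57% |
| 0.7 | 97% | 77% | 65% |

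Adjustment raises both models. The gap at the central cut stays at about 20 points.

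**5. Other predictors.** The 0.5 SD is a difference between arms. The article gives no effect or prevalence for any predictor. In the same simulations, logistic power for the covariate itself ran from 50% (r = 0.25, 16% v 31% cut) to about 100% (r = 0.7). No single figure can be attached to predictors, although the same information is discarded for them.

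**The case against.** The strongest reply is that nothing the trial is sized for is affected. The sample size, the primary outcome and the between-group tests all stay on the numerical scale, and the article never claims 80% power for the success/failure models. This stands. A reader might infer that the cut undermines the main comparison, and it does not.

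A second reply is that the logistic models are for prediction: odds ratios are a by-product, arm is not guaranteed a place under the selection rule, and sensitivity and specificity need a binary outcome. This also stands. It is a reason to keep the models. It also means they are poorly placed to be the only source of adjusted estimates, which is how the article leaves them.

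A reader might further infer that every adjusted effect and predictor drops to 55–60% power. The article does not support that. It plans no predictor effect and states no cut, and that range is an unadjusted figure for the arm effect at fairly central cuts.

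Finally, the article is condensed, and a full analysis plan may contain linear models and justified cuts. Their absence is not held against it. The point rests on the method the article does state for estimates corrected for other variables.

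**Conclusion.** The point holds as an avoidable loss of efficiency in a secondary analysis. For an arm effect of 0.5 SD with 63 per arm, power is 79.5% on the full scale, at most about 60% after a cut without adjustment, and lower as the success definition becomes stricter or more lenient. With one covariate at r = 0.25 it is about 63% (logistic, central cut) against about 83% (linear). These figures assume normal scores, equal SDs and a two-sided 5% test, with cuts and correlations that are assumed. The change is worth making because it is cheap, but the trial's main conclusion does not depend on it.

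**What to change.** In the Statistical analysis section, state that adjusted treatment effects and predictors of response will be estimated by linear regression of the numerical score or its change, with arm always included plus the chosen baseline variables. Report adjusted mean differences and predictor slopes with confidence intervals. Keep the success/failure logistic models as supportive responder and prediction analyses, including sensitivity and specificity, and say that they are not the adjusted treatment-effect analysis. If the full plan already contains such linear models, a sentence giving them this role is enough.

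The cost is some wording and one extra set of models in R, with no new patients or data. The downside is that a mean difference is less directly readable as a chance of success than a responder result, which is a reason to keep the responder models alongside.

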### Outcomes variables

All variables will be measured before the intervention, after the intervention (week 11), at six months, and a year. Flowchart of the study can be seen in Fig. 3.

**Fig. 3 Fig3:**
[figure not shown]
Flowchart of the study

#### Initial personal and sociodemographic variables

Age (in years)SexHealth CentreLevel of studies (no studies, basic education, secondary school, university studies)Employment situation (student, active, active in temporary disability, unemployed, domestic occupation)Marital status (single, widowed, couple, separated or divorced)Weight (kg), height, body mass Index (weight [kg]/height [m^2^]), and abdominal perimeter.Time since the onset of symptoms (months)Pain areas (McGill pain maps) [60]

#### Main outcomes variables

The primary outcome measure will be the difference between groups in health-related quality of life changes at different times. The Spanish version of the health Survey SF-36 V2 will be used [61, 62]. SF-36 is a 36-item scale built to assess health status and quality of life. It produces a profile of eight levels of functional health and wellness scores, as well as a summary of psychometric-based mental and physical health. Each scale transforms directly into a scale of 0–100. Higher scores indicate a better quality of life in general.

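### The primary outcome is the whole SF-36 at three follow-up visits with no score or visit selected, so the stated 5% error and 63 per group belong to no identified primary comparison

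*Protocol article*

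**What the plan says.** Under Main outcomes variables, the primary outcome is a between-group difference in SF-36 v2 change, with the timing left plural: "The primary outcome measure will be the difference between groups in health-related quality of life changes at different times". The same section describes what the questionnaire yields: "It produces a profile of eight levels of functional health and wellness scores, as well as a summary of psychometric-based mental and physical health". It does not say which of these scores carries the primary conclusion.

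Under Outcomes variables, the schedule is: "All variables will be measured before the intervention, after the intervention (week 11), at six months, and a year". That gives three post-baseline visits, none marked as primary.

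The Statistical analysis section plans two-group tests of means for numerical variables (Student's t, or Wilcoxon–Mann–Whitney when far from normal), with one threshold: "It will be considered as statistically significant *p*-values lower than 0.05". It gives no rule for what counts as success on the primary outcome.

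The Sample size calculation section is written for numerical variables in general: "A total of 63 individuals by each group of treatment will allow detecting, in numerical variables". The target is half a standard deviation at 80% power, and the error rate is described as "keeping the type I error at a 5% level". The section names neither the SF-36 nor a visit.

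**The concern.** A primary endpoint exists so that one pre-stated comparison, with a known error rate, decides the main question. Here the primary outcome is an instrument and a set of visits. Read at its widest, that is 10 scores × 3 visits = 30 comparisons, each with its own 5% threshold. A reader of the final report could not tell whether the score and visit put forward as primary had been chosen in advance or after seeing the results.

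Much is meant to rest on the result. The Discussion says that the findings could help change first-level care for chronic pain and that the sample size may support solid conclusions. It also makes a follow-on imaging study depend on positive clinical results.

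**Working it through.** **1. Reproduce the plan's own figure.** Inputs from the Sample size calculation section: d = 0.5, power 80%, type I error 5%. Sidedness is not stated.

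- Normal approximation, two-sided: n = 2(1.960 + 0.842)² / 0.5² = 62.8, so 63 per group. This matches the document.
- One-sided would give 50, so the plan is two-sided.
- The exact t calculation gives 63.8, so 64; with 63 per group, power is 79.5%.

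The stated size is therefore right, to within one patient per group, for one comparison at two-sided 5%.

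**2. Count the comparisons that the primary outcome covers.** Eight scales plus two summaries make 10 scores. Three post-baseline visits give 10 × 3 = 30.

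**3. Error rate if any one of the 30 could count, with no true effect.** If the tests were independent:

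- Either direction: 1 − 0.95³⁰ = 78.5%.
- Favouring the programme only: 1 − 0.975³⁰ = 53.2%.

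The tests are in fact correlated, and the document gives no correlations. The values below are assumptions. They use multivariate normal test statistics with a common correlation between scores crossed with a common correlation between visits. An event is |Z| > 1.96 at least once, or Z > 1.96 at least once for results favouring the programme.

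| Score correlation / visit correlation (assumed) | At least one significant, either direction | At least one favouring the programme |
|---|---|---|
| 0 / 0 | 79% | 53% |
| 0.3 / 0.5 | 68% | 38% |
| 0.5 / 0.7 | 53% | 27% |
| 0.7 / 0.7 | 41% | 21% |
| 0.8 / 0.8 | 31% | 15% |
| One test only | 5% | 2.5% |

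**4. Narrower readings of the primary outcome (either direction).** The range runs from very high correlation (0.8) to independence.

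- Two summaries at three visits, 6 tests: 15% to 1 − 0.95⁶ = 26.5%, so about 15% to 27%.
- One score at three visits, 3 tests: 10% to 1 − 0.95³ = 14.3%, so about 10% to 14%.

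Of these readings, only one named score at one named visit returns the 5% used in the sample size.

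**The case against.** The strongest reply has four parts.

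*The sample size statement is per comparison.* It speaks of a difference between a pair of group means, and on those terms it reproduces. A reader might infer that the stated 5% is false. The document does not support that: it claims no control over a family of tests. What stands against the plan is that the figure is attached to no particular comparison.

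*No success rule is written.* A reader might infer that the plan declares success on whichever score and visit crosses 0.05. It does not say so; the p < 0.05 sentence is a general threshold. The list of scores describes what the questionnaire produces and is not headed as ten endpoints. So the figures for 30 tests are conditional on a reading that the text leaves open. The narrower readings give smaller rates, though still above the nominal level.

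*Direction matters.* A reader might take the 41% to 68% as the chance of a false success. It is not, because it also counts significant results in which the programme does worse. The matching figure for results in its favour is 21% to 38%, against 2.5%.

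*The Discussion names a high bar.* It mentions an effect above 0.8 as a possible starting point for changing care. With 63 per group, an observed |d| above 0.8 has p of about 0.00002, so fewer than 0.1% of null trials would reach it even across 30 independent tests. But that is a benchmark for practice across the different variables measured, not a decision rule for the primary outcome.

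An unseen full protocol or analysis plan may also hold the testing order, the longitudinal model or a multiplicity adjustment, and their absence from an article is no fault. The identity of the primary endpoint is different. The article states it, and states it as a whole instrument at several times.

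**Conclusion.** The point holds as a defect in how the primary endpoint is defined: no SF-36 score and no visit is selected, so the 5% and the 63 per group are correct for one test and belong to no identified primary one. Confidence in this is high, because it rests on the text alone, and it should be corrected before the results are analysed.

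The size is conditional on two assumptions that are not in the document: that any one of the 30 comparisons could be taken as meeting the primary objective, and the correlations between scores and visits. The range must therefore be quoted with its direction and assumptions, and no single figure can be given as the trial's actual false-positive rate.

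**What to change.** Before any unblinded look at the data, name one SF-36 score at one visit as the single primary endpoint, tested at two-sided 5%. The choice is the sponsor's; the physical component summary at one year is only an example. Rewrite the sample size sentence so that the effect of 0.5 SD and the 63 per group refer to that endpoint. List the other SF-36 scores and visits as secondary or supportive, reported with confidence intervals. If confirmatory claims on any of them are wanted, test them in a fixed sequence after the primary or under a Holm correction.

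This changes wording only and needs no new patients, visits or data. The price is that a significant result on another scale or visit can no longer be called a primary success.
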